### Intervention: Brazilian Samba Protocol

The dance protocol will consist of dance classes, which will be conducted in a spacious room with appropriate facilities for a dance class for individuals with PD (floor without deformities, chairs for resting, and stereo with moderate volume to allow everyone to clearly hear the music). The classes will last for 1 hour, twice a week in the evening, for 12 weeks. The rhythm chosen for the classes is the Brazilian samba (two-four rhythm), as it was identified that its high resemblance to tango in the strong marking and the basic forward-backward steps can help development of balance and muscle tone of individuals. Furthermore, as a known national rhythm, appreciated by most of the population, it should facilitate obtaining participants’ compliance with the protocol. All classes will be divided into warm-up, main part, and relaxation. The activities will start with typical, 10-minute warm-up for ballroom dances suggested by Hackney and Earhart [9], including light walking to the rhythm of pre-selected music (samba), focusing on the breath, followed by light exercise of upper limb movement (rotation, abduction, and adduction), while always working on the musicality and rhythm, as well as postural alignment. During the main part of the lesson, the participants will follow the teacher/researcher instructions. The teacher will first demonstrate the step to be taught in that class, and the participants will initially execute it without a partner. Next, they will be paired up and perform the requested activity. The main part of the lesson will last 35 minutes, and partners will change every 7 minutes. This is aimed at facilitating practice with the largest possible number of pairings to develop motor skills and balance and to improve the adaptation to change process. During the lessons, activities will be divided into (1) following the commands of the teacher, or (2) dancing freely. The steps to be taught are described in Table 2. The sequences of classes and selected songs, including the steps, are shown in Multimedia Appendix 1.

**Table 2 table2:** Description of the steps to be taught.

Steps	Feature execution
Presentation of Rhythm	During the class, traversing movements with songs of different speeds will be executed, to familiarize students with the rhythm.
Basics Steps	One step forward, two steps in place, and a step back.
Ginga^a^	With one foot forward and one foot back, the students shift their weight between the front and back legs without moving.
Working with Rhythm	Adapting previously learned movements and steps to songs of different rhythms and speeds.
“X”^a^	The pair forms an X, to perform the basic step forward. The gentleman goes on the side of the lady.
Cruzado^a^	Starting in the position of X, the pair faces each other and returns to the X position.
Bate e Volta^a^	Starting in the starting position, the lady and gentleman move away from each other and return to the starting position.
Steps Sequence	Students repeat the learned steps in predefined sequence, first pausing after each step, until they will are able to perform them with music.
Samba no pé^a^	Steps taken individually focusing on shifts at different rhythms.
Giro da Dama^a^	Starting with the backwards basic step, the gentleman leads the lady to make the turn, the lady holds the rotation moving forward, and the gentleman accompanies her movement walking forward at her side.
Review of Steps	At random, a review with all learned steps will be performed to enhance learning and improve step implementation.
Prom	During the free dancing session, music of different speeds and rhythms will be included. Students will be dancing together, and the pairs will be encouraged to swap with every song to practice the already-learned steps.

^a^The steps names were maintained in their original language.

The songs were divided, according to the beats per minute (bpm), into three movements: slow (40-72 bpm), medium (72-120 bpm), and fast (120-208 bpm) [18]. The beats analysis was performed with BPM Detector Pro.

At the end of every class, calm exercises will be performed for 5 minutes to promote relaxation after activity, involving massage, stretching, or a slow walk with quiet music in the background.

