#### Control Group

The data collection for the control group will be held simultaneously to the intervention group of the period. The researcher will schedule a visit to the patient’s home or other preferred place, where they will clarify the goals of the study, emphasize the importance of keeping to normal daily activities, and request that the patient avoids starting a physical activity during these 12 weeks. The subjects in the control group will also be advised that not performing physical activity for 12 weeks is against the guidance for prevention of disease and maintenance of health, and therefore, it is only a guideline.

The participants in the control group will be invited to monthly lectures that address the maintenance of health, prevention of falls, and psychological care. They will be asked, in person, about their general health and performance of daily activities. During the interview after the 12 weeks of data collection, any subjects who state that they have started a regular physical activity of any type will be excluded from the control group. At the end of the study, all participants (control and intervention) will receive a booklet stating, in a clear and objective way, the main results for both the group and individually (including the activities started during the period and the option to be excluded from the databank). Since the dance classes will continue after the end of the study, all participants will be invited to take part in them.

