### Statistical Analysis and Sample Size

Sample size was based on primary outcomes and calculation performed with the G*Power 3.1.9.2 software [28], assuming a moderate effect of Brazilian samba on motor signals (UPDRS III), according to Cohen [29] with 0.447 effect size. We chose a more cautious effect size because there is still no evidence of Brazilian samba in DP rehabilitation. However, due to the effects already found in similar interventions (ref=-0.62/-0.55) [30] as described in the meta-analysis by Lutzke et al, a significant effect is expected regarding to motor symptoms. We used alpha=.05 and power of 0.9, applied in two groups (experimental group and control group) analyzing the results through a two-way analysis of variance (ANOVA) with repeated measures and Sidak post-hoc comparison test for a comparative analysis into and between groups. Significance level will be set at 5%. Anticipating 25 individuals in each group, but foreseeing a sample loss of around 20% [31,32], we have chosen to include 30 individuals per group, ending with a total of 60 subjects.

After the intervention, the data will be transferred to SPSS v. 20.0. First, descriptive statistics will be performed (mean, standard deviation, and percentage). Two-way ANOVA with repeated measures and Sidak post-hoc comparison test will be used for a comparative analysis of the results of the control group with the experimental group and of the within-group changes between pre- and postintervention period. Significance level will be set at 5%.

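### Samba is taught in group classes, but the planned ANOVA and the 90% power assume independent participants, so the 5% level and the stated power hold only if there is no class-level correlation

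*Protocol article*

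**What the plan says.** Under Intervention: Brazilian Samba Protocol, every session is a class held in one room with shared music. "During the main part of the lesson, the participants will follow the teacher/researcher instructions", and after practising a step alone the dancers are paired: "The main part of the lesson will last 35 minutes, and partners will change every 7 minutes". Two one-hour classes a week for 12 weeks make 24 sessions.

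Under Control Group, contact is mainly individual: "The researcher will schedule a visit to the patient’s home or other preferred place". Controls are also invited to monthly lectures, which is about three optional shared occasions over the 12 weeks.

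Under Statistical Analysis and Sample Size, the power statement reads "We used alpha=.05 and power of 0.9, applied in two groups (experimental group and control group"), with the effect given only as "with 0.447 effect size". The numbers follow: "Anticipating 25 individuals in each group, but foreseeing a sample loss of around 20" percent, then "we have chosen to include 30 individuals per group, ending with a total of 60 subjects". The analysis is fixed as "Two-way ANOVA with repeated measures and Sidak post-hoc comparison test will be used for a comparative analysis of the results". The only inflation of the sample size is for loss to follow-up. Neither the sample size nor the analysis includes a class or teacher term, an ICC or a design effect.

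**The concern.** The design is partially nested: one arm is treated in groups and the other essentially is not. Dancers in a class share a teacher, a room, music and each other. The Discussion presents the lively environment and social interaction as part of how the programme works, so correlated changes among classmates are a plausible result of the design. The shared class and teacher are the main source of dependence; changing partners mainly spreads it across the class.

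A repeated-measures ANOVA handles the pre-post pairing within a person. It does not handle correlation between persons. If classmates' changes are positively correlated, the standard error of the group x time effect is too small, its interval is too narrow, and the test rejects too often.

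If all dancers form one class, the class and teacher effect is also fully confounded with the samba effect. The Introduction nevertheless presents the programme as a possible treatment option for people with Parkinson's disease generally.

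**Working it through.** **Inputs from the article.** Alpha 0.05, power 0.9, effect size 0.447, 25 evaluable and 30 enrolled per group, two groups, two time points.

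**Inputs assumed, because the article does not give them.** Class-level ICC on change scores of 0.01, 0.05 or 0.10; one, two, three or five classes of equal size; clustering in the dance arm only.

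**1. The plan's own figure.** The 25 per group can be matched but not confirmed, because the effect-size metric, the test family and the pre-post correlation (rho) are not stated. For N = 50 in total:
- 0.447 as Cohen's f, between-groups test, noncentrality f² x N x 2/(1 + rho): power 91.2% at rho 0.75 and 90.4% at rho 0.80. This matches the stated 90%.
- 0.447 as f, group x time test, noncentrality f² x N x 2/(1 - rho): at rho 0, 0.1998 x 50 x 2 = 19.98, power 99.2%; above 99.9% at rho 0.5.
- 0.447 as a standardised difference d: 35% power with 25 per group.

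All these readings treat participants as independent.

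**2. Type I error of the unadjusted group x time test.** With two time points this is a two-sample comparison of change scores. With m dancers per class:
- dance-arm design effect DE = 1 + (m - 1) x ICC
- variance inflation of the between-arm contrast V = (DE + 1)/2
- true type I error = 2 x [1 - Phi(1.96/sqrt(V))]

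For one class of 25 and ICC 0.05: DE = 1 + 24 x 0.05 = 2.20; V = (2.20 + 1)/2 = 1.60; 1.96/sqrt(1.60) = 1.55; type I error = 12.1%.

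| Classes | m | ICC 0.01 | ICC 0.05 | ICC 0.10 |
|---|---|---|---|---|
| 1 | 25 | 6.4% | 12.1% | 18.6% |
| 2 | 12.5 | 5.7% | 8.4% | 11.8% |
| 3 | 8.3 | 5.4% | 7.2% | 9.4% |
| 5 | 5 | 5.2% | 6.2% | 7.4% |

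A simulation of 40,000 trials with the ordinary t test gave 6.5%, 12.3% and 19.1% for one class, so the normal approximation is adequate. At ICC zero nothing changes.

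**3. Power under the readings of the stated effect.** One class, ICC 0.05:
- Group x time, f = 0.447: dividing the noncentrality by 1.60 leaves 93% at rho 0 and 99.8% at rho 0.5.
- Between-groups test on the average of pre and post: a class effect can arise only after baseline. With the ICC defined on the post score, it adds 0.05/4 x 24/25 = 0.012 to a contrast variance of 2 x 0.9/25 = 0.072 (rho 0.80), an inflation of 1.17. Power is about 86% and type I error about 7%.

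The direction is the same under each reading; the size is not.

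**The case against.** **The consequence is conditional.** It depends on an ICC and a class count that the article does not give, and it runs from negligible (five classes, ICC 0.01: 5.2%) to large (one class, ICC 0.10: about 19%). This stands. A reader might infer that the stated error rate and power are simply wrong; the documents support only that they hold if the class ICC is zero.

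**A specific lower power.** A reader might also infer that power falls from 90% to about 73% (one class, ICC 0.05). That figure comes from solving for the standardised difference that gives 90% with 25 per arm (0.936) and dividing its noncentrality by sqrt(1.6). The plan states 0.447, not 0.936, and the readings above give 93% or more for group x time and about 86% for the between-groups test. The 73% is not derivable from the plan.

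**Controls are not wholly unclustered.** They share the monthly lectures. This is true, but it is a far lighter exposure than 24 partnered classes, and any clustering among controls would add further variance.

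**One class has no analytic cure.** The inflated error rate refers to a null about classes and teachers in general; for the effect of this one class as delivered, it does not apply. This stands, and it makes the one-class remedy a limit on the conclusion plus a sensitivity analysis.

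**Detail left out of an article.** The number of classes may be in the full protocol or in the multimedia appendix, neither of which is shown, so its absence is not the fault. The point rests on what the article does state: a test and a power claim that both assume independence.

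**Conclusion.** The concern holds as a conditional one. The article fixes group delivery in one arm and an analysis and power claim that assume independent participants, so the nominal 5% and 90% apply only at a class ICC of zero. For any positive ICC the unadjusted test is anti-conservative and its intervals are too narrow. Across the assumed ICC range of 0.01 to 0.10, the true level of the group x time test is about 6% to 19% with one class, 6% to 12% with two and 5% to 9% with three. These figures assume 25 evaluable per arm, equal classes and independent controls. The loss of power cannot be quantified for this plan. The correction is worth making because it is cheap, but it does not show that the trial is underpowered or that its test is invalid whatever the class structure.

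**What to change.** - Record which class each dancer attends and state the number and size of classes.
- If there are several classes, report the group x time effect from a partially nested mixed model: group, time and their interaction fixed, person random, a class-by-time random effect in the dance arm only, and small-sample degrees of freedom. With only two or three classes, present this as a sensitivity analysis beside the ANOVA, since the class variance then rests on one or two degrees of freedom.
- If there is one class, keep the ANOVA and add intervals re-computed for ICC 0.01, 0.05 and 0.10 in the dance arm. With 25 per arm the standard error is multiplied by sqrt(1.12) = 1.06, sqrt(1.60) = 1.26 and sqrt(2.20) = 1.48. State that the result applies to this class and teacher, whose effect cannot be separated from that of samba.
- In Statistical Analysis and Sample Size, say that the 90% power assumes no class clustering. Do not insert a replacement figure unless the effect-size metric, test family and pre-post correlation are also stated.

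The cost is one recorded variable and a few lines of text, with no extra participants. The downside is wider intervals and few degrees of freedom for the class variance.

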### Statistical Analysis and Sample Size

Sample size was based on primary outcomes and calculation performed with the G*Power 3.1.9.2 software [28], assuming a moderate effect of Brazilian samba on motor signals (UPDRS III), according to Cohen [29] with 0.447 effect size. We chose a more cautious effect size because there is still no evidence of Brazilian samba in DP rehabilitation. However, due to the effects already found in similar interventions (ref=-0.62/-0.55) [30] as described in the meta-analysis by Lutzke et al, a significant effect is expected regarding to motor symptoms. We used alpha=.05 and power of 0.9, applied in two groups (experimental group and control group) analyzing the results through a two-way analysis of variance (ANOVA) with repeated measures and Sidak post-hoc comparison test for a comparative analysis into and between groups. Significance level will be set at 5%. Anticipating 25 individuals in each group, but foreseeing a sample loss of around 20% [31,32], we have chosen to include 30 individuals per group, ending with a total of 60 subjects.

After the intervention, the data will be transferred to SPSS v. 20.0. First, descriptive statistics will be performed (mean, standard deviation, and percentage). Two-way ANOVA with repeated measures and Sidak post-hoc comparison test will be used for a comparative analysis of the results of the control group with the experimental group and of the within-group changes between pre- and postintervention period. Significance level will be set at 5%.

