**Methods:**

The sample will be selected at random from individuals diagnosed with PD in the city of Florianopolis (SC, Brazil). Sample size calculation was performed with the G*Power 3.1.9.2 software, with 0.447 effect size, at 5% significance level, power of 0.9, and test and sample loss of 20%. This yielded 60 individuals divided between the intervention and control groups. The questionnaires will be filled out before and after the dance intervention. The data collection for the control group will be held simultaneously to the intervention group. The classes will last for 1 hour, twice a week in the evening for 12 weeks, and all classes will be divided into warm-up, main part, and relaxation. Two-way analysis of variance with repeated measures and Sidak post-hoc comparison test will be used for a comparative analysis of the final results of the control group with the experimental group and of the within-group changes between pre- and postintervention period.

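### The 90% power claimed at an effect size of 0.447 does not fit its cautious label unless a very high, unstated pre-post correlation is assumed

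*Protocol article*

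**What the plan says.** The section Statistical Analysis and Sample Size describes the calculation as "assuming a moderate effect of Brazilian samba on motor signals (UPDRS III), according to Cohen [29] with 0.447 effect size". It justifies the value with "We chose a more cautious effect size because there is still no evidence of Brazilian samba in DP rehabilitation" and sets it beside results from a cited meta-analysis: "due to the effects already found in similar interventions (ref=-0.62/-0.55". The error rate and power follow: "We used alpha=.05 and power of 0.9, applied in two groups (experimental group and control group". The planned analysis is stated as "analyzing the results through a two-way analysis of variance (ANOVA) with repeated measures and Sidak post-hoc comparison test", with assessments before and after 12 weeks. The result is 25 per group, raised to 30 per group (60 in total) for about 20% loss. The software is G*Power 3.1.9.2.

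The abstract repeats the inputs: "with 0.447 effect size, at 5% significance level, power of 0.9, and test and sample loss of 20"%.

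The article does not say whether 0.447 is Cohen's f or a standardised mean difference d, which ANOVA term was powered, or what pre-post correlation was assumed.

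**The concern.** The paragraph makes three statements together: the effect is moderate, it is more cautious than earlier results of 0.55 to 0.62, and 25 per group detects it with 90% power. Comparing 0.447 with 0.55 and 0.62 makes sense only if all three figures are on one scale. G*Power's ANOVA routines work in f, and for two equal groups f is half of d. If an f was compared with values of d, an optimistic assumption has been described as a cautious one. If 0.447 is a d, the sample size looks small for 90% power.

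At stake is how the UPDRS III result is read. A reader who takes the paragraph at face value will treat a non-significant result as coming from a trial with a 10% chance of missing a modest effect. Depending on the correlation, that chance could be much larger.

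**Working it through.** **Inputs from the article.** Effect size 0.447; alpha 0.05; power 0.90; two equal groups; 25 per group (N = 50); two assessments; comparison values 0.55 and 0.62 (absolute).

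**Assumptions.** Two-sided test; equal SDs across groups and times; 0.55 and 0.62 are standardised mean differences. The article does not say this last point, but the negative signs and the direct comparison with 0.447 suggest it. Correlations (rho) from 0.5 to 0.9 are shown because none is given. Power uses the noncentral F (or equivalent t) with N − 2 error degrees of freedom.

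**Step 1. Reproduce the plan's figure with 0.447 as f.** f² = 0.447² = 0.1998.

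- Plain two-group comparison: noncentrality = f² × N = 0.1998 × 50 = 9.99, power 87%. For 90%, N = 56 (28 per group).
- Repeated measures, group term averaged over both assessments: noncentrality = f² × N × 2/(1 + rho). At rho = 0.8 this is 0.1998 × 50 × 2/1.8 = 11.10, power 90.4%. N = 50 is the smallest even total for rho from about 0.76 to 0.82; at rho = 0.5 it is 42.
- Repeated measures, group-by-time term: noncentrality = f² × N × 2/(1 − rho). At rho = 0.5 only N = 16 is needed, so this routine with f = 0.447 does not explain 50.

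So 25 per group can be reproduced, exactly or nearly, with 0.447 as f.

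**Step 2. What f = 0.447 means.** For two groups, d = 2f = 2 × 0.447 = 0.894. Cohen's conventional large mark for f is 0.40, so 0.447 is above it. Against the cited values, 0.894/0.62 = 1.44 and 0.894/0.55 = 1.63, that is, 44% and 63% larger. For the group-by-time term, the same f is a still larger difference in change: 4f = 1.79 SD of a single score.

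**Step 3. Treat 0.447 as d.** Let d be the between-group difference in change divided by the SD of a single score. The SD of change is √(2(1 − rho)) times that SD, so the effect tested is d/√(2(1 − rho)) and its noncentrality is that value × √(25/2).

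| rho | power, d = 0.447 | power, d = 0.55 | power, d = 0.62 |
|---|---|---|---|
| 0.5 | 34% | 48% | 57% |
| 0.7 | 52% | 69% | 79% |
| 0.8 | 69% | 85% | 92% |
| 0.9 | 93% | 99% | more than 99% |

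At rho = 0.5 the SD of change equals the SD of a single score, so the first row also applies to a comparison of post-treatment values alone. There, d = 0.447 needs 107 per group for 90% power.

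**Step 4. Correlation needed for 90%.** With 25 per group, 90% power requires a difference of 0.936 SD of change. Solving d/√(2(1 − rho)) = 0.936 gives rho = 1 − (d/0.936)²/2:

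- d = 0.447: 1 − (0.4776)²/2 = 0.886
- d = 0.55: 0.83
- d = 0.62: 0.78

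**The case against.** The strongest reply is that the sample size is not shown to be wrong. Step 1 recovers 50 patients with 0.447 as f, and Step 4 recovers 90% power with 0.447 as d at a high correlation. Patients must be on stable medication doses and are reassessed after only 12 weeks, so a high correlation is not excluded. This stands, and it rules out several stronger readings that a reader might infer.

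- That 25 per group gives 90% power only for a large effect, or that the stated power is absent. The article gives no correlation, and at about 0.89 even d = 0.447 reaches 90%.
- That the trial is well powered only for effects far above those it cites. At rho = 0.8, power is 85% for d = 0.55 and 92% for d = 0.62.
- That the wrong ANOVA term was powered. The group term averages over the pre-treatment assessment and so would not isolate the samba effect, but the article does not say which routine was run. A match at rho of about 0.8 is not evidence of use.

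It can also be said that G*Power settings are detail that an article leaves to the full protocol. Their absence alone would not be a point. The point is that the article states a power and a justification for it, and readers will rely on both.

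**Conclusion.** The point holds in conditional form. If 0.447 is f, the sample size is roughly as stated, but moderate and more cautious are wrong: the effect is d = 0.894, above the large mark. The 44% to 63% excess over the cited effects further assumes that those are standardised mean differences. If 0.447 is d, the labels are fair, but power for the difference in change runs from 34% to 93% over correlations of 0.5 to 0.9, and 90% needs about 0.89. The documents do not settle which reading applies. In either case, the cautious justification and the 90% power agree only at a very high correlation that is not declared.

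This is a defect in the stated justification, not a demonstrated failure of the design. It should be corrected, but it ranks below an essential change because neither the sample size nor the analysis has to move.

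**What to change.** Keep 60 patients and rewrite the sample-size paragraph:

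1. State that the powered term is group-by-time, whether 0.447 is f or d, and which pre-post correlation was assumed, with its source.
2. If 0.447 is f, delete both moderate and more cautious. If it is d, they may stay, provided the correlation is given.
3. Replace the unconditional 90% with, for example: *25 completers per group give 90% power (two-sided 5%) for a between-group difference of 0.94 SD of change; at d = 0.447, power is 34% to 93% for pre-post correlations of 0.5 to 0.9.* The corresponding figures for 0.55 and 0.62 could be added.
4. Make the abstract agree.

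The cost is one paragraph and one sentence of the abstract, with no extra patients and no change to the analysis. The downside is that the stated power becomes less favourable.

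### Thirty per group less the planned 20% loss leaves 24 completers, not the 25 in the sample-size statement; the cost is small

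*Protocol article*

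**What the plan says.** The Statistical Analysis and Sample Size section gives the inputs as "We used alpha=.05 and power of 0.9, applied in two groups", with a moderate effect on the UPDRS III "according to Cohen [29] with 0.447 effect size" and the planned analysis as "analyzing the results through a two-way analysis of variance (ANOVA) with repeated measures". The size before loss follows: "Anticipating 25 individuals in each group". The allowance for loss is then made: "foreseeing a sample loss of around 20% [31,32], we have chosen to include 30 individuals per group", for a total of 60.

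The Methods paragraph of the abstract repeats the effect size, significance level and power. It gives the loss as 20%, without the word for approximately, and concludes: "This yielded 60 individuals divided between the intervention and control groups".

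Neither place prints the formula that leads from 25 to 30. Neither gives a pre-post correlation, or says whether the powered effect is the group main effect or the group-by-time interaction.

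**The concern.** The 25 per group comes straight after the significance level, power and effect size and before the allowance for loss, so it reads as the number wanted at the end of the study. An allowance for a given loss should leave that number when the loss occurs. Here it does not: at the plan's own loss rate each group ends one short.

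The allowance matters in this design because losses come directly out of the analysed sample. The Participants section lists failure to complete all stages among the exclusion criteria, and the Control Group section removes controls who report having started regular physical activity. The margin between 25 and 30 is what protects the number on which the stated power rests.

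**Working it through.** **Inputs, all from the Statistical Analysis and Sample Size section:** 25 per group before loss, loss of about 20% (exactly 20% in the abstract), 30 per group enrolled, effect size 0.447, alpha 0.05, power 0.9, two groups, repeated-measures ANOVA. Two time points (before and after the intervention) follow from the Data Collection section.

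**Step 1: reproduce the plan's figure.** 25 × (1 + 0.20) = 25 × 1.2 = 30 per group, 60 in total. This matches exactly.

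**Step 2: apply the planned loss to the enrolled number.**
- Per group: 30 × (1 − 0.20) = 24, against 25.
- In total: 60 × 0.8 = 48, against 50.

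**Step 3: the enrolment that would keep 25.** n/(1 − loss) = 25/0.8 = 31.25, so 32 per group and 64 in total (50/0.8 = 62.5, so 63 if only the total is rounded up).

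**Step 4: the loss that 30 per group can absorb.** (30 − 25)/30 = 5/30 = 16.7%.

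**Step 5: the cost in power.** Two assumptions are needed: that 0.447 is Cohen's f, and a value for the pre-post correlation ρ. For the between-factors test with m = 2 time points and total N, the noncentrality is λ = f² × N × m / (1 + (m − 1)ρ), with 1 and N − 2 degrees of freedom, and f² = 0.447² = 0.1998. For example, at ρ = 0.75:
- N = 50: λ = 0.1998 × 100/1.75 = 11.42
- N = 48: λ = 0.1998 × 96/1.75 = 10.96

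| ρ | Power, N = 50 | Power, N = 48 | Smallest even N for 0.9 |
|---|---|---|---|
| 0.50 | 0.947 | 0.938 | 42 |
| 0.70 | 0.919 | 0.908 | 48 |
| 0.75 | 0.912 | 0.900 | 50 |
| 0.80 | 0.904 | 0.892 | 50 |
| 0.90 | 0.888 | 0.875 | 52 |

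Of the correlations tried, 0.75 and 0.80 are those at which the plan's total of 50 is the smallest even total reaching 0.9. There the loss of two completers costs about 1.2 points.

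For the group-by-time interaction, λ = f² × N × m / (1 − ρ). Power with 48 is then 0.990 at ρ = 0 and above 0.999 at ρ = 0.5, so the shortfall has no practical effect on that test.

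**The case against.** **The body says about 20%, and 30 is presented as a choice.** A loss of 16.7% might be called about 20%, and 25 may simply have been rounded up to 30. This softens the mismatch but does not remove it. The abstract states a flat 20%, an approximate 20% covers values on both sides, and 30 works only at 16.7% or below.

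**The error in the formula is not shown.** A reader might infer that 25 was multiplied by 1.2 instead of being divided by 0.8. The exact match suggests it, but no formula is printed and rounding fits as well. The objection stands as far as the cause is concerned. The shortfall in Step 2 does not depend on the cause.

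**The loss of power is not established.** A reader might infer that the design misses its stated power of 0.9. The documents do not support that: the correlation and the tested effect are not given, and with 24 per group power stays above 0.9 at lower correlations or for the interaction. A single-time comparison of two groups at f = 0.447 gives 0.872 with 25 per group and 0.858 with 24, but it equals the between-factors test only at a correlation of 1. It is not the analysis the plan names, and it is below 0.9 before any loss, so it does not measure the effect of the loss step. This objection stands in full.

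**Conclusion.** The three stated figures (25 before loss, 20% loss, 30 enrolled) are inconsistent. At 20% loss 24 per group remain, and the allowance covers 16.7%. That conclusion needs only the article's own numbers and the usual reading of loss as a share of those enrolled.

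The consequence is small: one completer per group and, with f = 0.447 in the between-factors test at a correlation of 0.75 to 0.80, about 1.2 points of power, ending between 0.900 and 0.892. Those power figures rest on an assumed metric, correlation and test. The point is minor and gives no reason to change the design or to enrol more participants.

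**What to change.** Keep 60 participants and correct the statement:

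- In Statistical Analysis and Sample Size, say that 30 per group allows for a loss of up to 16.7% (5 per group), and that 24 per group remain if the loss is 20%.
- Give the power for 24 per group under the same G*Power test and correlation that produced 25, and name both.
- In the abstract, stop attributing the total of 60 to a 20% loss.

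The cost is a sentence or two in the methods and a phrase in the abstract. Recruitment, design and analysis are unchanged; the stated loss allowance becomes slightly less favourable.
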